## Study Population

Outpatients with fluctuating hearing diagnosed as PDS in *SLC26A4* genetic testing are eligible to participate if all of the inclusion criteria described below are met, and if none of the exclusion criteria below are met.

[Inclusion Criteria]

1) Aged at least seven and below fifty years at the time of consent

2) Confirmed PDS-positive by genetic testing such as Sanger Sequencing

3) Report of subjective symptoms of fluctuating hearing disorder in a medical interview for case registration

4) Subjective symptoms of episodes of hearing loss and/or dizziness/vertigo within one year prior to the case registration

5) Had undergone inner-ear function testing at least three times, including standard pure-tone audiometry, performed with an interval of one day or longer, within six months prior to the case registration

6) Voluntary informed consent in writing obtainable from the patient or the patient’s legally acceptable representative

[Rationale]

1) To allow participation of patients of a wide range of ages, in consideration of patient demographics

2) through 5) To select patients who are considered to be appropriate for evaluation of investigational product efficacy

6) To ensure ethical conduct of the clinical trial

[Exclusion Criteria]

1) Prior use of molecular targeted drugs related to mTOR pathway, such as sirolimus, other mTOR inhibitors (e.g., everolimus) and tyrosine kinase (e.g., bevacizumab, sorafenib)

2) History of hypersensitivity to sirolimus, including sirolimus derivatives, and its additive agents

3) HBs antigen-positive, HBs antibody-positive, HBc antibody-positive, or active hepatitis C (HCV antibody-positive patients with inactive hepatitis and with normal-range values of liver function do not apply.)

HBs antigen-positive patients for which the cause is presumed to be due to vaccination against hepatitis B may participate in this clinical trial.

4) Severe blood abnormalities or hepatic dysfunction that demonstrate conditions shown below.

| Items | Value |
| --- | --- |
| AST or ALT | 100 IU/L or higher |
| Hematocrits | below 30% |
| Platelet count | below 80,000/mm^3^ |
| Absolute neutrophil count | below 1,000/mm^3^ |
| Total white blood cell count | below 3,000/mm^3^ |

5) Patients with poorly controlled dyslipidemia

Serum triglyceride of 500 mg/dL or higher or LDL cholesterol level of 190 mg/dL or higher despite being under treatment for dyslipidemia.

6) Severe renal impairment

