# Administration of Investigational Products

Figure 1 Dosing Protocol

Phase I (single-blind): NPC-12T placebo tablets for 3 months (12 weeks)

Phase II (double-blind): NPC-12T active substance tablets or NPC-12T placebo tablets for 6 months (24 weeks)

[Dosage at the outset of the trial]

Subjects weighing less than 40 kg will take one 1-mg tablet orally once every other day.

Subjects weighing 40 kg or more will take one 1-mg tablet orally once per day.

The investigational products are to be taken before sleep.

The bodyweight measured at V1 will be referred to in determining dosage throughout the trial.

<Rationale for the dosing time>

The package insert of Rapamune 1 mg tablets was referred to when setting the dosing time. The insert cites reports that state administration of the tablet after a high-fat meal increased the blood concentration of sirolimus. To reduce effects of high-fat meals, the dosing time of the investigational products is set to be before sleep.

[Prescription of the investigational products]

In Phase I (V1, V2, V3, and V4) and Phase II (V5 and V6), the principal investigator or subinvestigator will prescribe investigational products in accordance with the dosage at the start of the trial described above.

In Phase II (V7, V8, V9, V10, and V11), the unblinded doctor will instruct the principal investigator and subinvestigators on the prescription of the investigational product based on the criteria for dosage change. The principal investigator or subinvestigator will make a judgment on whether dosage reduction is required or dosage increase is permissible, taking account of subjects’ safety, including risks of adverse events. If the conditions are deemed appropriate, the principal investigator or subinvestigator will prescribe the investigational products as instructed by the unblinded doctor. The unblinded doctor will provide instructions to the principal investigator or subinvestigator in accordance with the trough concentration measurements and the prescription schedule generated by the randomization manager. The trough concentration measurements and the prescription schedule are not to be disclosed to any person except the unblinded CRCs until the end of the trial, and will be kept securely locked in a cabinet accessible only to the unblinded doctor.

[Criteria for dosage change]

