## Statistical Analysis of Efficacy

Assessment of efficacy in this trial is regarded as a secondary objective. With regard to continuous endpoints, summary statistics of changes or percentage changes based on actual measurements and from baseline at each point in time will be calculated for each dosage arm. A one-sample *t*-test will be used for comparison between actual measurements and baseline values at each point in time for each dosage arm. The two-sided 95% confidence interval for average change for each dosage arm will then be estimated. Using a two-sample *t*-test, the change or percent change at each point in time between the two arms will be compared. The two-sided 95% confidence interval for average difference between the two arms will be estimated. If the data is found to be non-normal, use of nonparametric methods and statistical methods based on probability distribution other than normal distribution will be considered. With regard to binary endpoints, a contingency table will be compiled for each point in time, and Fisher’s exact test will be applied in making comparison of the distribution in the two dosage arms. The Clopper-Pearson method will be applied to estimate the two-sided 95% confidence interval for each dosage arm. The difference in the two-sided 95% confidence interval will be estimated using the normal approximation.

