### Efficacy Endpoints

[Secondary Endpoints]

1) Frequency of hearing loss episodes (number of occurrences per year)

2) Highest measurement of auditory threshold shift at a hearing loss episode (dB)

Definition of hearing loss episodes: Hearing loss episodes with subjective symptoms and episodes detected as audiometric data will be counted as hearing loss episodes in this trial. Concerning audiometric data, audiometric testing of four different frequencies for right and left ears will be performed, and the average of measurements obtained at five recent time points will be defined as the baseline. A change of 10 dB or more observed in the testing period including the screening phase will be identified as an episode. The period from the beginning of the episode until the condition returns to the baseline will be counted as one episode. Episodes observed in left and right ears or in different frequencies concurrently will be considered as separate episodes.

3) Frequency of dizzy spells (number of occurrences per year)

Dizzy spells in which the subject is conscious are to be counted.

4) Maximum amplitude (°/sec) and maximum frequency (cycle/sec) of nystagmus in a hearing loss episode

5) Percentage of cases in which increase in hearing threshold was observed during remission in the observation period (comparison of measurements at the end of Phase I and the end of Phase II)

6) Improvement in threshold during remission

7) Shorter duration of hearing loss episodes

8) Alleviation of symptoms of dizziness/vertigo

Changes in total scores of the Dizziness Handicap Inventory from Phase I to Phase II

9) Percentage of cases in which equilibrium exacerbated during remission in the observation period (comparison of measurements at the end of Phase I and the end of Phase II)

[Exploratory Endpoints]

1) Reduction in endolymphatic hydrops (MRI findings)

2) Inhibition of goiter or thyroid enlargement

3) Cell biological changes in thyrocytes detected by cytology tests

4) Comparison of results of in vitro efficacy evaluation of inner ear cells derived from PDS-specific iPS cells and of clinical evaluation

5) Deviation from threshold value for frequency of abnormalities of auditory brain stem responses and for pure-tone audiometry

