## Target Study Sample Size

A sample size of 16 subjects is expected to be studied: 12 subjects for NPC-12T active substance arm, and 4 subjects for NPC-12T placebo arm.

[Reason for choice of sample size]

As this clinical trial will focus on a rare disease, and is exploratory, feasibility was the main aspect that was considered in setting the sample size. In terms of safety analysis, provided that clinically significant adverse events exist, the size is sufficient to detect adverse events of 15% incidence with 85% accuracy. In terms of efficacy analysis, when making a comparison of NPC-12T arms concerning hearing test endpoints of periods without treatment and with treatment, a difference can be detected at 80% power (two-sided 5% significance level), if the number of evaluable subjects is 11 and Cohen’s d for endpoints is 0.85.

In estimation of correlation coefficient between evaluation indices, if data of two arms are integrated for evaluation, and the number of evaluable subjects having population correlation coefficient of 0.7 (i.e., medium to high degree of correlation) is 13, then a difference can be detected at a minimum of 80% power (two-sided 5% significance level).

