## Significance Level and Multiplicity

The level of significance used for all analyses in this trial is to be two-sided 5%. The confidence coefficient of confidence interval is to be two-sided 95%. As the efficacy analysis in this trial is for a secondary purpose, multiplicity of different endpoints and time points will not be adjusted.

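### The between-arm efficacy test omits the Phase I covariate and allows percent change where Phase I can be zero; whole-phase maxima, if used, would distort the within-arm comparison

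*Protocol*

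**What the plan says.** Protocol, Statistical Analysis of Efficacy: continuous endpoints get a one-sample t-test against baseline within each arm. Between arms, a two-sample t-test is used in which "the change or percent change at each point in time between the two arms will be compared". No covariate is named, and nothing says which endpoints take change and which take percent change. If data prove non-normal, nonparametric or other-distribution methods are to be considered.

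Efficacy Endpoints: frequencies of hearing loss episodes and dizzy spells are per year. Endpoint 2 is "Highest measurement of auditory threshold shift at a hearing loss episode (dB"), and endpoint 4 is the maximum amplitude and frequency of nystagmus in an episode. No rule combines several episodes in one patient. Concurrent events in different ears or audiometric frequencies count as separate episodes.

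Administration of Investigational Products: Phase I is 12 weeks of placebo for everyone. Phase II is "NPC-12T active substance tablets or NPC-12T placebo tablets for 6 months (24 weeks").

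Study Population: entry requires "Subjective symptoms of episodes of hearing loss and/or dizziness/vertigo within one year prior to the case registration".

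Target Study Sample Size: "12 subjects for NPC-12T active substance arm, and 4 subjects for NPC-12T placebo arm". For untreated v treated periods the section claims 80% power in a two-sided test at 5%, on the condition "if the number of evaluable subjects is 11 and Cohen’s d for endpoints is 0.85".

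**The concern.** The trial collects a 12-week run-in on every patient, and the named between-arm test uses it only by subtraction. With four placebo patients, chance imbalance at baseline is large, and subtraction is the best correction only when the two phases are highly correlated.

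Percent change is allowed for endpoints that can be zero in Phase I. Patients with a zero would leave that analysis according to their baseline value, and with 16 patients each loss matters.

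The two phases differ in length. The sample-size argument rests on comparing the untreated with the treated period, and a maximum over the longer period is expected to be larger even if nothing has changed. That would hide benefit in a trial whose stated purpose includes exploring which endpoints to use later.

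**Working it through.** **The protocol's own figure.** Within-arm comparison, n = 11, d = 0.85, two-sided 5%: Φ(0.85 × √11 − 1.96) = Φ(0.859) = 0.805, so the stated 80% reproduces as a normal approximation. The one-sample t-test that the protocol names gives 72% (noncentral t, 10 df). This is the comparison that part (c) concerns.

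**(a) Covariate.** From the protocol: 12 v 4. Assumed: equal variance σ² in both phases and correlation ρ, which the protocol does not give.
- SD of the chance baseline difference: σ√(1/12 + 1/4) = 0.58σ.
- Change-score variance: 2(1 − ρ)σ². ANCOVA residual variance: (1 − ρ²)σ². Ratio: (1 + ρ)/2.
- The price of estimating the slope with N = 16 is about 1 + 1/(16 − 4) = 13/12.

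| ρ | (1 + ρ)/2 | × 13/12 |
|---|---|---|
| 0.2 | 0.60 | 0.65 |
| 0.5 | 0.75 | 0.81 |
| 0.7 | 0.85 | 0.92 |
| 0.8 | 0.90 | 0.975 |
| 0.9 | 0.95 | 1.03 |

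Break-even: (1 + ρ)/2 = 12/13, so ρ = 0.846. Simulation at 12 v 4 gives 0.65, 0.81, 0.92, 0.96 and 1.04 for the same rows. For a true difference of 0.85 outcome SDs, power goes from 28% to 33% at ρ = 0.5 and from 42% to 45% at ρ = 0.7.

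**(b) Zero in Phase I.** From the protocol: 12 weeks. Assumed: independent Poisson attacks at yearly rate λ. P(none) = exp(−12λ/52).

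| λ per year | P(none in 12 weeks) | P(at least 1 of 12 active patients has none) |
|---|---|---|
| 2 | 63% | >99% |
| 4 | 40% | >99% |
| 6 | 25% | 97% |
| 12 | 6% | 54% |

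Percent change divides by zero for these patients. Raw change in the annualised rate is defined for all, and phase length does not bias it (within-arm rejection under no effect 4.9-5.6% in simulation).

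**(c) Whole-phase maximum.** Assumed: Poisson attacks, and peaks of 10 dB plus an exponential with mean 10 dB. With μ attacks expected in a phase, the mean maximum among patients with at least one is 10 + 10·Ein(μ)/(1 − e^(−μ)), where Ein(μ) is the integral from 0 to μ of (1 − e^(−u))/u. Here μ = 12λ/52 in Phase I and 24λ/52 in Phase II.

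| λ per year | Phase I (dB) | Phase II (dB) | Shift with no effect (dB) | Patients with an episode in both phases |
|---|---|---|---|---|
| 4 | 22.40 | 24.85 | 2.5 | 51% |
| 8 | 24.85 | 29.37 | 4.5 | 82% |
| 12 | 27.21 | 32.99 | 5.8 | 93% |

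If 11 patients are evaluable, the within-arm t-test rejects about 7-8%, 13% and 18% of the time instead of 5%. If 12 are enrolled and only those with an episode in both phases are evaluable, it rejects about 5% at 4 per year (few pairs remain, although the shift does) and 18% at 12 per year. Between arms, the simulated test keeps its level (4.5-5.6%) with a mean difference near 0, because both arms have the same two phase lengths.

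**The case against.** The case against is substantial, and several parts stand.

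- A reader might infer that the Phase I value is thrown away. It is not: a change score uses it with slope 1. The gain from ANCOVA depends on an unknown correlation and vanishes near 0.85.
- A reader might infer that the efficacy analysis as a whole breaks down at zero. It does not. Raw change is offered alongside percent change, and the fallback clause admits count distributions. But that clause is triggered by non-normality, not by an undefined value, and percent change is still allowed without restriction.
- A reader might infer that every maximum endpoint is biased in the quoted comparison. The documents do not support that. Equal phase lengths in both arms cancel the effect between arms. Within arms it arises only under a whole-phase maximum, which the protocol does not state. The endpoint wording can equally mean a per-episode peak, and the rule may lie in the analysis plan. Nor does the power statement name maxima.
- Near-nightly home audiometry in two ears and four frequencies with a 10 dB trigger may make zeros rare for endpoint 1. That is possible, but separate counting of concurrent channels adds to the count without adding attacks, and P(none) depends on attacks. Dizzy spells have no such trigger.
- The shorter Phase I window might also truncate episode duration (endpoint 7). No size can be put on this, so no claim is made.

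The efficacy analyses are secondary and unadjusted for multiplicity, which limits what is at stake. It does not make this a matter left open: the protocol names the tests, and its section on deviations requires any other method to be reported as a change.

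**Conclusion.** The point holds in three limited parts.

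(a) The named between-arm test is less efficient than ANCOVA over most plausible correlations: about 35%, 19% and 8% more precise at 0.2, 0.5 and 0.7, no gain near 0.85, and a 3-4% loss at 0.9.

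(b) Percent change is unsuitable for any endpoint that can be zero in Phase I. Between 6% and 63% of patients could be lost from it at 12 down to 2 independent attacks per year.

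(c) Conditional on a whole-phase maximum, the within-arm comparison of endpoint 2 shifts by roughly 2.5-6 dB toward worsening at 4-12 attacks per year with no drug effect. Endpoint 4 would shift in the same direction, by an amount not quantified here.

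The correlation, the attack rates, the Poisson form and the peak distribution are assumptions; the protocol gives none of them.

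**What to change.** 1. Between arms, make ANCOVA (Phase II value on arm plus Phase I value) the analysis for continuous endpoints, with the t-test on change as supportive.
2. Do not use percent change for endpoints that can be zero. Analyse episode and dizzy-spell frequency as annualised rates by a method robust to overdispersion: negative binomial or quasi-Poisson with log observed time, or a rank or permutation test. An exact Poisson split of events between the phases is not suitable, because concurrent ears and frequencies are counted separately. If, say, each attack registers in four channels, the variance is fourfold and a nominal 5% test rejects 2 × [1 − Φ(1.96/√4)] = 33% of the time.
3. For within-arm comparison of endpoints 2 and 4, use the mean of per-episode peaks, or compare Phase I with an equal 12-week window such as weeks 24-36. Give whole-phase maxima descriptively only. A phase without an episode still yields no peak, so report the number of evaluable patients.

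The change is one of wording, to be made before unblinding. It costs one degree of freedom, a small loss of precision if the correlation is about 0.9, and fewer nights of data if equal windows are chosen.

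### Fisher's exact test for the binary efficacy endpoints is valid but runs at a true level of at most 1 to 2% with 12 v 4 subjects; a pre-specified Boschloo test is never less powerful and still holds 5%

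*Protocol*

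**What the plan says.** For each binary endpoint, section 17.3 (Statistical Analysis of Efficacy) asks for a table at every time point and fixes one between-arm method, saying that Fisher's "exact test will be applied in making comparison of the distribution in the two dosage arms". The same section allows other methods when continuous data are non-normal, but names no alternative for binary data.

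Two secondary endpoints in 17.3.1 are expressly proportions:
- endpoint 5: "Percentage of cases in which increase in hearing threshold was observed during remission in the observation period"
- endpoint 9: "Percentage of cases in which equilibrium exacerbated during remission in the observation period"

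Section 17.5 plans "12 subjects for NPC-12T active substance arm, and 4 subjects for NPC-12T placebo arm". Section 17.6 states: "The level of significance used for all analyses in this trial is to be two-sided 5" per cent.

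On the weight of these analyses, 17.3 says "Assessment of efficacy in this trial is regarded as a secondary objective", and 17.6 adds that "multiplicity of different endpoints and time points will not be adjusted".

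**The concern.** Fisher's test conditions on the total number of events. With only four placebo subjects, few tables are possible for any given total, so the p-value moves in large steps and the test seldom gets close to the 5% it is allowed. Endpoints 5 and 9 have no other between-arm test in the protocol, so any power lost here falls on the only randomised test of those endpoints.

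For example, suppose all four placebo subjects worsened and 4 of 12 on sirolimus did. Fisher's test would give p = 0.077, while an exact test that also holds 5% gives p = 0.034. A change of test made after seeing the first figure would not be credible, so the choice has to be settled in advance.

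**Working it through.** **Inputs.** Arm sizes 12 and 4 (17.5); two-sided 5% (17.6); Fisher's test (17.3). The protocol states neither event rates nor power for a binary endpoint. The rates below are therefore assumptions, and the only figure to compare with is the nominal 5%.

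**Method.** There are 13 x 5 = 65 possible tables (a events of 12 on active, b of 4 on placebo). For a rejection region R and a common rate p, the true level is the sum over R of C(12,a) C(4,b) p^(a+b) (1-p)^(16-a-b), maximised over p. Power uses the same sum with separate rates for the two arms. The Boschloo p-value of a table is the maximum over p of the probability of all tables whose two-sided Fisher p-value is no larger. Given the total, that probability never exceeds the Fisher p-value, so the Boschloo p-value cannot exceed it either and no Fisher rejection can be lost.

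**Fisher p-values at the boundary.**
- 0/12 v 2/4: 6/120 = 0.050 exactly
- 2/12 v 3/4: (264 + 12)/4368 = 0.063
- 4/12 v 4/4: (495 + 495)/12870 = 0.077

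**Fisher's true level at 12 v 4.**
- Rejecting at p < 0.05: maximum 1.10%, near p = 0.34.
- Rejecting at p <= 0.05: maximum 1.96%, near p = 0.16 and its mirror. Only 0/12 v 2/4 and its mirror make the difference.

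**Boschloo's true level at 12 v 4.** The region is all Fisher rejections plus 0/12 v 2/4, 2/12 v 3/4, 4/12 v 4/4 and their mirror images. The maximum is at p = 0.5. The tables in which placebo is worse contribute C(12,a) C(4,b) as follows:

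6 + 4 + 1 + 48 + 12 + 264 + 66 + 220 + 495 = 1116

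Doubling for the mirror images gives 2232/65536 = 3.41%. The Boschloo p-values are 0.020 for 0/12 v 2/4, 0.028 for 2/12 v 3/4 and 0.034 for 4/12 v 4/4.

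**Power at 12 v 4 (assumed rates, active v placebo).**

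| Rates | Fisher, p < 0.05 | Fisher, p <= 0.05 | Boschloo |
|---|---|---|---|
| 20% v 80% | 43.8% | 44.9% | 61.9% |
| 25% v 75% | 27.2% | 27.9% | 43.8% |
| 30% v 90% | 34.8% | 34.9% | 54.9% |
| 25% v 90% | 47.2% | 47.3% | 66.8% |
| 10% v 75% | 58.6% | 64.6% | 75.0% |
| 30% v 60% | 9.3% | 9.8% | 18.6% |
| 30% v 50% | 5.2% | 5.7% | 11.4% |

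**Other evaluable numbers, first five scenarios.**

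| Active v placebo | Fisher maximum level | Boschloo maximum level | Power gain (points) |
|---|---|---|---|
| 12 v 4 | 1.1% (2.0%) | 3.4% | 10 to 20 |
| 11 v 4 | 1.7% | 2.3% | 0 to 7 |
| 12 v 3 | 1.8% | 4.9% | 1 to 17 |
| 10 v 4 | 1.5% | 2.8% | 9 to 18 |
| 11 v 3 | 1.3% | 3.9% | 17 to 23 |

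**Version of the test.** A Boschloo test that doubles the one-sided p-value is a different procedure. At 12 v 4 it adds only 4/12 v 4/4 and its mirror to what Fisher rejects at p <= 0.05, with a level of 2.6%. Its power is 50.3% for 20% v 80% and 34.0% for 25% v 75%.

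**The case against.** Fisher's test is a standard, valid choice for sparse tables. The 5% in 17.6 is a ceiling, and a test that stays below it complies. A reader might infer from a true level of 1 to 2% that the plan misstates its significance level or that its error control has failed. The documents support neither: nothing is misstated, and the false-positive rate is lower than allowed, not higher. That part of the objection stands in full.

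A reader might also infer that about 20 points of power are being thrown away whatever happens. That does not hold either. The upper figure belongs to large differences at exactly 12 v 4, and appears again at 11 v 3. Section 17.5 itself reckons with 11 evaluable active subjects for its within-arm comparison. At 11 v 4 four of the five scenarios gain about one point or less, and 4/11 v 4/4 has a Boschloo p-value of 0.051. Of the six tables added at 12 v 4, three are mirror images in which sirolimus does worse. A fourth, 0/12 v 2/4, is new only if Fisher's p of exactly 0.05 would not have counted.

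The stakes are modest. Efficacy is a secondary objective, feasibility drove the sample size, multiplicity is unadjusted, and only two of nine secondary endpoints are expressly proportions. These facts limit the weight of the point. They do not remove it, because the alternative is exact, holds 5% and never rejects less.

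**Conclusion.** The point holds as one of avoidable inefficiency. At the planned 12 v 4, Fisher's test uses roughly a fifth to two fifths of the permitted error rate (1.1/5 to 2.0/5). Boschloo's test in the stated version uses about two thirds (3.4/5) and stays below 5%. On assumed rates the benefit at 12 v 4 is about 10 to 20 points of power for differences of 50 to 65 points, about 9 points for 30% v 60%, and about 6 for 30% v 50%. With other evaluable numbers the benefit in the large-difference scenarios ranges from almost nothing to 23 points. No choice of rates or arm sizes makes it negative. Even with the better test, power stays below 80% in every scenario shown, so the change does not make these comparisons adequately powered. The enumerated levels do not depend on the assumed rates; the power figures do.

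**What to change.** In 17.3, replace Fisher's exact test for the between-arm comparison of binary endpoints with Boschloo's exact unconditional test. State that it is two-sided, that tables are ordered by the two-sided Fisher p-value, and that rejection is at p <= 0.05.

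Name this one test and leave no option of an unconditional score test. The two share a rejection region at 12 v 4 but part at other sizes: at 11 v 4 with 30% v 90% their powers are 55.2% (score) and 40.8% (Boschloo). An open choice would let significance depend on the test picked.

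The cost is one sentence, settled before unblinding, with no extra patients or data. There is some programming: stock software may implement the version that doubles the one-sided p-value, so the specified ordering may need a short validated program. The values 0.028 for 2/12 v 3/4 and 0.034 for 4/12 v 4/4 can serve as checks.

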# Target Study Sample Size

A sample size of 16 subjects is expected to be studied: 12 subjects for the NPC-12T active substance arm, and 4 subjects for the NPC-12T placebo arm.

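### The normal-approximation interval for the difference in proportions falls well short of 95% coverage with 12 v 4 patients and can disagree with the planned Fisher test

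*Protocol*

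**What the plan says.** Section 17.3 of the protocol (Statistical Analysis of Efficacy) gives three methods for binary endpoints:

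- Between-arm test: "Fisher’s exact test will be applied in making comparison of the distribution in the two dosage arms".
- Interval within each arm: "The Clopper-Pearson method will be applied to estimate the two-sided 95% confidence interval for each dosage arm".
- Interval for the difference: "The difference in the two-sided 95% confidence interval will be estimated using the normal approximation".

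The third sentence is awkwardly worded. The only sensible reading is the 95% interval for the difference between the two arms' proportions.

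Section 17.5 (Target Study Sample Size) sets "12 subjects for NPC-12T active substance arm, and 4 subjects for NPC-12T placebo arm". Section 17.6 sets two-sided 5% significance and 95% confidence throughout, without multiplicity adjustment. In section 17.3.1, secondary endpoints 5 and 9 are percentages of patients who worsen (higher hearing threshold, poorer equilibrium), so they fall under these rules, as would any other binary efficacy endpoint.

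**The concern.** The plan treats the arms as too small for large-sample methods in two of the three binary analyses, then uses a large-sample method for the third. It is the weakest place to do so, because the standard error of the difference depends on a proportion estimated from 4 patients. Whenever placebo gives 0/4 or 4/4, its estimated variance is zero and the interval carries no placebo uncertainty at all.

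The method is named in the protocol, so this is not a detail left to the statistical analysis plan. The fallback for non-normal data in section 17.3 comes before the binary methods and concerns continuous endpoints; none is given for the difference in proportions. At stake is an interval labelled 95% that is too often wrong, printed beside a Fisher p-value that it may contradict, in a trial meant to inform later protocols.

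**Working it through.** **Inputs.** n1 = 12 and n2 = 4 (section 17.5); nominal level 95%, so z = 1.96 (section 17.6); interval by normal approximation (section 17.3). The last is read as unpooled without continuity correction, since none is stated. The protocol gives no event rates, so true rates are assumed and varied.

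**Formula.** With d = p1 − p2, the limits are d ± 1.96 × √[p1(1 − p1)/12 + p2(1 − p2)/4].

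**One table by hand: 3/12 active v 0/4 placebo.**
- d = 0.25; SE = √(0.25 × 0.75/12 + 0) = 0.125; interval 0.25 ± 0.245 = 0.5% to 49.5%, excluding zero.
- Fisher: with 3 events among 16 patients, the probabilities of 3, 2, 1 and 0 events on active are 220/560, 264/560, 72/560 and 4/560. The two-sided p is (220 + 72 + 4)/560 = 0.53.

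The mirror table, 9/12 v 4/4, gives −49.5% to −0.5% with the same p. For 0/12 v 0/4 the SE is zero and the interval is [0, 0].

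**Exact coverage.** There are 13 × 5 = 65 possible tables. For each pair of true rates, coverage is the sum of Binomial(12, p1) × Binomial(4, p2) probabilities over tables whose interval contains p1 − p2. Over true rates 0.1 to 0.9 in steps of 0.1 (81 pairs):

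| | Lowest | Highest | Mean |
|---|---|---|---|
| Stated in the plan | 95% | 95% | 95% |
| Normal approximation | 56.6% | 92.1% | 81.3% |
| Newcombe hybrid score | 91.2% | 98.3% | 95.1% |

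The stated 95% is not reached at any of the 81 pairs. The minimum, at 10% active v 20% placebo (true difference −0.10), shows the cause. If placebo is 0/4, the lower limits for 0, 1, 2 and 3 active events are 0, −0.073, −0.044 and +0.005, and for more events they are higher still. None reaches −0.10. Placebo is 0/4 with probability 0.8⁴ = 41%, so coverage cannot exceed 59%.

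**Equal true rates: how often zero is wrongly excluded, and in which direction.**

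| True rate, both arms | Coverage | Excludes zero | Active looks worse | Active looks better | Placebo 0/4 or 4/4 |
|---|---|---|---|---|---|
| 10% | 91.0% | 9.0% | 7.3% | 1.7% | 66% |
| 15% | 83.7% | 16.3% | 13.8% | 2.5% | 52% |
| 20% | 78.7% | 21.3% | 18.1% | 3.2% | 41% |
| 30% | 77.1% | 22.9% | 18.0% | 4.9% | 25% |
| 50% | 84.1% | 15.9% | 8.0% | 8.0% | 12.5% |

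Rates above 50% mirror those below with the directions exchanged: at 70%, active looks worse in 4.9% and better in 18.0%.

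**Agreement with Fisher.** In 18 of 65 tables the interval excludes zero while Fisher p ≥ 0.05 (two of them at exactly p = 0.05); in 12 of the 18 placebo is 0/4 or 4/4. The reverse conflict never occurs. With a 30% rate in both arms, Fisher rejects in 1.1% of trials and the interval excludes zero in 22.9%.

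**Newcombe alternative.** With Wilson limits (l, u) for each arm, the limits are d − √[(p1 − l1)² + (u2 − p2)²] and d + √[(u1 − p1)² + (p2 − l2)²].
- 3/12 v 0/4: Wilson limits are 0.089 to 0.532 and 0 to 0.490. Lower limit 0.25 − √(0.161² + 0.490²) = −0.27; upper limit 0.25 + 0.282 = 0.53. Zero is included.
- 0/12 v 0/4: a Wilson upper limit at zero events is z²/(n + z²), so 3.84/15.84 = 0.24 and 3.84/7.84 = 0.49. The interval is −49% to 24%, not a single point.
- Conflict with Fisher falls from 18 to 8 tables. One that remains is 7/12 v 0/4: 2.7% to 80.7% with p = 0.088.

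**The case against.** **Limited reach.** Efficacy is a secondary objective without multiplicity adjustment, so no confirmatory claim rests on this interval. The primary safety analysis uses Clopper-Pearson limits per arm (section 17.4.1) and is untouched. The powered efficacy comparison is within patients, untreated v treated, not active v placebo. No dosing, stopping or monitoring rule uses the interval, and Fisher's p and the exact per-arm limits are reported too. All of this stands and lowers the severity. It does not make a nominal 95% interval correct.

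**Range of coverage.** A reader might take a range such as 70% to 91% as the true coverage. It describes 77 of the 81 pairs on this grid but is not a bound: coverage is 56.6% at 10% v 20% and 97.6% at 5% v 5%. Only a range tied to stated rates can be defended.

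**False efficacy signal.** A reader might infer that the interval manufactures evidence of benefit. The protocol does not support that in general. Endpoints 5 and 9 count worsening, so 3/12 v 0/4 is active doing worse. At equal rates of 15% to 30%, false harm occurs in 13.8% to 18.1% of trials and false benefit in 2.5% to 4.9%, against a nominal 2.5% on each side. False benefit dominates only when worsening is common, and the protocol gives no rates to show which applies.

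**Disagreement with Fisher.** Some disagreement between an interval and a conservative exact test is normal and is not in itself an error. The fault is the undercoverage, which makes the disagreement frequent.

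**Another normal approximation.** A continuity correction would raise coverage to 81.2% to 99.7% on the same grid, but the protocol does not state one.

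**Conclusion.** The sentence is wrong as written, with moderate severity. For true rates of 10% to 90% in each arm, an interval labelled 95% covers 56.6% to 92.1% of the time (mean 81.3%), and with equal rates it wrongly excludes zero in 9% to 23% of trials. These are false differences in either direction, not specifically false efficacy. The figures assume the unpooled interval without continuity correction, full 12 v 4 data and the stated grid of rates. Losing one placebo patient would make the worst case worse: 12 v 3 gives about 45% to 92%.

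**What to change.** Replace the last sentence of section 17.3 with: *The two-sided 95% confidence interval for the difference in proportions between the two arms will be calculated by the Newcombe hybrid score method.*

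This costs one sentence and no patients or data. If made by amendment before unblinding, it is part of the plan; otherwise section 17.8 requires the change to be reported in the clinical study report.

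There are two consequences to accept. The Newcombe interval is wider in all 26 tables where placebo is 0/4 or 4/4 (3/12 v 0/4: width about 0.80 instead of 0.49), which is where the planned interval is too short. It is narrower in the other 39 (10/12 v 1/4: 0.820 − 0.053 = 0.767, instead of 1.057 − 0.109 = 0.948, with an upper limit no longer above 100%). And 8 of 65 tables will still exclude zero with Fisher p ≥ 0.05, so the report should say that the interval and the test are built differently. Only an interval obtained by inverting the test would remove that entirely.
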